### Fidelity criteria

Attendance and notes on reasons for absence at individual visits and group consultation is made after each session. Compliance to registration of steps is made monthly and reasons for failing to register steps is tracked and noted. Notes from the MI talk are registered in the health journal. The project group has regular meetings to discuss issues regarding MI talks, physical activity on prescription and measurements, in order to assure the routines of both measurements and intervention components. The quality of each individual counseling session is assessed on a 1-10 scale by the diabetes specialist nurse for both motivational interviewing and physical prescription. A qualitative study to explore how the participants perceived the support as well as barriers and facilitators will help to evaluate the intervention efficacy from a patient perspective.

### Sample size and planned statistical analysis

The sample size calculation assumed 80 % power and was calculated drawing on previous literature [14, 66] by statistical power analysis. To detect a difference of > 0.6 mmol/mol in HbA_1c_ with a standard deviation of 1.2 % at 12 months between group A and B and between group A and C we need 56 per group. Taking account the compliance and drop-out (30 %) and patients which decline participation (20 %) we need in group A 100 patients, in group B 100 patients and in group C 110 patients.

The study will be evaluated with both quantitative and qualitative methods and a cost-effectiveness analysis will be performed. The CONSORT 2010 statement will be used for description and analysis [45]. Data will be analyzed following the Intent-to-treat approach (ITT). Descriptive statistics will be used to describe the study population at baseline. The study data will be examined for outliers, normality and missing data. Potential confounders as (e.g. BMI at baseline, gender and age) will be used if there are differences at baseline.

Un-paired and paired tests, correlation coefficients as well as ANOVAs will be used to assess the bivariate effects of the interventions and to analyze within-group and between-group differences and changes. In addition, logistic regression models and/or cluster analyses will be performed to analyze issues related to dose–response and responder characteristics. SPSS 22 (SPSS Inc., Chicago, IL, USA) will be used for the statistical analysis.

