**Biomarkers**									
HbA_1c_ (mmol/mol)	✓		✓		✓		✓		✓
Plasmaglucose (fasting) mmol/l	✓		✓		✓		✓		✓
Triglycerides (mmol/l)	✓		✓		✓		✓		✓
LDL (mmol/l)	✓		✓		✓		✓		✓
HDL (mmol/l)	✓		✓		✓		✓		✓
Total Cholesterol (mmol/l)	✓		✓		✓		✓		✓
Free fatty acids (mmol/l)	✓		✓		✓		✓		✓
Insulin (mU/l)	✓		✓		✓		✓		✓
IGF BP1 (μ/l)	✓		✓		✓		✓		✓
ApoA1 (g/l)	✓		✓		✓		✓		✓
ApoB (g/l	✓		✓		✓		✓		✓
C-peptid (pmol/l)	✓		✓		✓		✓		✓

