#### Biomarkers

Measurements include fasting blood samples on HbA_1c_ (mmol/mol), plasma glucose (mmol/l), triglycerides (mmol/l), LDL (mmol/l), HDL (mmol/), total Cholesterol (mmol/l), free fatty acids (mmol/l), Insulin (mU/l), IGF BP1 (μ/l), Apolipoprotein-A1 (g/l), Apolipoprotein B (g/l) and C-peptid (nmol/l). HbA1c, haemoglobin A1c (ref < 5.2 %) is determined with immunologic MonoS method, Unimate (Roche Diagnostics, Basel, Schweiz). To convert HbA1c MonoS into HbA1c (DCCT) NGSP (National Glycoprotein Standardization Programme) the formula, NGSP = 0.92*MonoS + 1,33 is used. Plasma glucose are determinedwith a glucose oxidase method, total Cholesterol and triglycerides are determined by using enzymatic method, LDL and HDL are determined by using a homogeneous method, Apolipoprotein-A1 and Apolipoprotein B are determined by using turbimetric method and C-peptid are determined by using immunometric method using two monoclonal antibodies and detection with electrochemiluminiscense using a Modular E system (Beckman Coulter, Inc.). Serum insulin concentrations are determined with RIA-kits purchased from Pharmacia & Upjohn, Stockholm. IGFBP-1 concentrations in serum are determined by RIA according to the method of Póvoa et al. [50]. Samples are saved for later free fatty acid analyses.

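### The sample-size sentence puts the HbA1c difference in mmol/mol and its SD in percent, and 56 per group is not reproduced from the printed inputs

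*Protocol article*

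**What the plan says.** All of the following is in the protocol article.

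- **Sample size and planned statistical analysis, power:** "The sample size calculation assumed 80 % power and was calculated drawing on previous literature". No alpha, sidedness or baseline adjustment is given.
- **Same section, target:** "To detect a difference of > 0.6 mmol/mol in HbA_1c_ with a standard deviation of 1.2 % at 12 months".
- **Same section, result:** "between group A and B and between group A and C we need 56 per group". The section then allows 30 % for compliance and drop-out and 20 % for patients who decline, and arrives at 100 in A, 100 in B and 110 in C.
- **Biomarkers and Table 1:** the outcome is listed as "HbA_1c_ (mmol/mol"). The eligibility limits for pre-diabetes are also in mmol/mol.
- **Biomarkers, assay detail:** the laboratory method has a percent reference value, and "the formula, NGSP = 0.92*MonoS + 1,33 is used" converts one percent scale to another. No conversion between percent and mmol/mol is given.

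**The concern.** The target difference and the SD define the effect that the trial says it can detect on its primary outcome. With one in mmol/mol and the other in percent, their ratio has no meaning as printed. The article's own figures show that the scales are far apart: the pre-diabetes range lies between 39 and 47 mmol/mol, while the assay reference is below 5.2 %.

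Putting both figures on one scale does not settle the matter, because the usual formula then does not return 56 at 80 % power. The difference, the SD and the power are what a reader will use to judge a null result for A against B or A against C. If they are misprinted or do not agree with each other, that judgement has no sound basis.

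**Working it through.** **Inputs.** From the sample-size section: difference 0.6, SD 1.2, power 80 %, 56 per group, pairwise comparisons A–B and A–C, 30 % loss, 20 % declining, planned arms 100/100/110. Assumed, because not stated: both figures on one scale, two-sided alpha of 5 %, no baseline adjustment.

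**Step 1: effect size.** d = 0.6/1.2 = 0.5. The ratio is the same whichever single unit was meant.

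**Step 2: try to reproduce 56.** Normal approximation:

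n = 2(z₀.₉₇₅ + z₀.₈₀)²/d² = 2(1.960 + 0.842)²/0.25 = 62.8, so 63 per group.

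The t test gives 63.8, so 64 per group. The stated 56 is not reproduced.

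**Step 3: other tests, with d = 0.5.**

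| Test | n per group for 80 % | Power at 56 |
|---|---|---|
| Two-sided 5 %, t test | 64 | 74.6 % |
| One-sided 5 %, t test | 51 | 84 % |
| Three-group F test, 5 %, A differing from B and C by 0.6 | 59 | 78 % |
| Two-sided 2.5 % (two comparisons), t test | 78 | 65 % |

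The normal formula returns 56 at 75 % power, two-sided 5 %. With 56 per group and the two-sided 5 % t test, the difference detectable at 80 % power is 0.64.

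**Step 4: what could give 56 at 80 %.**
- Rounded inputs: 0.62 and 1.16 print as 0.6 and 1.2, and the t test then needs 55.9, so 56.
- Baseline adjustment with a correlation of about 0.33: 62.8 × (1 − 0.33²) ≈ 56.

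The article mentions neither.

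**Step 5: link to the planned arms.** 56/(0.7 × 0.8) = 100 exactly, so 56 is the figure carried into the planned size and not an isolated misprint. The same inflation applied to 64 gives 64/0.56 = 114.3, so 115 per group.

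**Step 6: power at the evaluable numbers (two-sided 5 % t test, d = 0.5).**
- Only the 30 % loss applies after randomisation: 100 × 0.7 = 70 and 110 × 0.7 = 77, so 70/70/77 remain. Power is 83.6 % for A–B and 85.3 % for A–C.
- The 20 % also comes off: 100 × 0.56 = 56 in A and B, and 110 × 0.56 = 61.6 in C. Power for A–B is 74.6 %.

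**The case against.** **The unit mismatch is a label slip.** The ratio of 0.5 strongly suggests that one scale was intended, and the article otherwise uses mmol/mol for eligibility and for the outcome. The percent values under Biomarkers are assay detail, and leaving out a further conversion formula is normal in an article. This stands: the outcome scale itself is not in doubt. The sentence that sets the target is still wrong as printed, and nothing elsewhere corrects it.

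**The 75 % is conditional.** Alpha, sidedness and adjustment are not stated, and a one-sided 5 % test would give 84 % at 56. The inputs are printed to one decimal and the difference as greater than 0.6, so rounding may account for the gap. This also stands. A reader might infer that the article proves 75 % power where it claims 80 %. It does not, because that conclusion needs the two-sided, unadjusted test and inputs of exactly 0.6 and 1.2.

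**The literal reading is not the intended one.** A reader might take the printed units at face value and infer that the trial claims to detect a difference some 11 times smaller than it can. That needs a conversion factor that the article does not give. Assuming 10 to 11 mmol/mol per percentage point, about 6,300 to 7,600 per group would be needed, and power at 56 would be about 6 %. These figures show how much the label matters. They do not describe the trial's design.

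**Replacing 56 by 64 would create a new inconsistency.** The article's own inflation would then give 115 per arm against 100 planned. This stands, so the remedy should not prescribe 64.

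**The trial may be large enough anyway.** If decliners are lost before randomisation, as the procedure section's wording about patients being included suggests, 70/70/77 remain and power exceeds 80 %. The timeline text even speaks of 310 participants completing. That limits the practical damage but does not make the printed sentence correct.

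**Conclusion.** The point holds in two parts of different strength.

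- **Certain, with no assumption:** the difference and the SD are printed on two HbA1c scales, so the stated effect size is wrong as written.
- **Conditional:** on one scale (d = 0.5), with an unadjusted two-sided 5 % t test, 56 per group gives about 75 % power and 64 are needed for 80 %. One-sided 5 % and the three-group F test do not return 56 either (51 and 59). Rounding or an unstated adjustment could explain the figure, so an arithmetic error is not proven. What is established is that the printed inputs do not reproduce 56.

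It would go too far to conclude that enrolment is too small. Under the same test, power is about 84 to 85 % if only the 30 % loss follows randomisation, and about 75 % for A–B if the 20 % also comes off. The article does not say which applies.

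**What to change.** In the sample-size section:

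1. State the difference and the SD on one named HbA1c scale, consistent with the mmol/mol used for the outcome.
2. State alpha, sidedness and any baseline adjustment, including the correlation assumed.
3. Either justify 56 per group with the unrounded inputs or the adjustment, or restate its power as about 75 %.
4. Say which of the two losses (30 % and 20 %) occur after randomisation, and give the power for A–B and A–C at the evaluable numbers that follow.

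The cost is wording, and possibly a slightly less favourable stated power. No extra enrolment is asked for, and conduct and analysis do not change.

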### Outcome measures

Measurements are made on all participants at week 0, 8, 12, 16, 24, month 9, 12, 18 and 24. The primary outcome variable is HbA_1c_. Health outcomes and measurement time points are summarized in Table 1. The measurements are planned to be performed within ± 2 weeks and notes are made if they are made sooner or later than this.

**Table 1 Tab1:** Outcome parameters and time points for measurements for all groups in Sophia Step Study

Variables	Baseline	Trial	Trial	Trial	Trial	Trial	Trial	Trial	Trial
		w. 8	w. 12	w. 16	6 m	9 m	12 m	18 m	24 m

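### The un-paired and paired tests and ANOVAs named for intervention effects do not by themselves deliver the promised intention-to-treat comparison of HbA1c; a mixed model on the scheduled values would

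*Protocol article*

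**What the plan says.** All the analysis statements stand in the protocol article under Sample size and planned statistical analysis.

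- Principle: "Data will be analyzed following the Intent-to-treat approach (ITT").
- Methods for effects: "Un-paired and paired tests, correlation coefficients as well as ANOVAs will be used to assess the bivariate effects of the interventions", covering differences and changes within and between groups. Logistic regression and cluster analysis are kept for dose–response and responder questions.
- Missing values: "The study data will be examined for outliers, normality and missing data". No rule for handling them follows.
- Expected loss: the inflation step begins "Taking account the compliance and drop-out" and gives 30% for the two together, with a separate 20% for patients who decline.

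Under Outcome measures, "Measurements are made on all participants at week 0, 8, 12, 16, 24, month 9, 12, 18 and 24". Table 1 there places HbA1c, the primary outcome, at baseline, week 12 and months 6, 12 and 24. The sample size refers to the 12-month differences A against B and A against C.

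**The concern.** An intention-to-treat comparison covers everyone randomised, in the group assigned. An un-paired test of 12-month HbA1c, or of change to 12 months, takes in only those with a 12-month value. An ANOVA over repeated visits, if that is what is meant, usually needs every visit it uses. With a sizeable loss planned for, the named tests and the stated principle fit badly.

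Two things are at stake. One is bias in the primary contrast, if those without a value would have done differently from those with one, and to a different degree by arm. The other is waste: a participant lost after month 6 already has up to three HbA1c values, and a 12-month two-group test either drops them all or, for that participant, cannot use them.

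Loss that differs by arm is plausible. Group A is offered 12 group meetings and 9 individual consultations, which groups B and C are not. Under Limitations the article expects participants to be highly motivated to change, so those given usual care may leave for other reasons than those in A.

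**Working it through.** **1. The plan's own figures.** The inflation step reproduces for A and B: 56 / (0.7 × 0.8) = 100. So the trial is sized on those who remain. The 110 for C does not follow from that formula. The 56 does not reproduce either: reading both 0.6 and 1.2 as HbA1c percentage points, two-sided 5% and 80% power give 2 × (1.96 + 0.84)² × 1.2² / 0.6² ≈ 63. That is a separate matter, and nothing below depends on it.

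**2. Upper bound on missing values.** If the whole 30% lacked a 12-month HbA1c, 0.30 × 310 = 93 would be missing and 70, 70 and 77 would remain. Power for 0.6 with SD 1.2 would be about 84% (A–B) and 86% (A–C), against 94% with 100 per arm complete. Power is therefore not the main worry; bias is.

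**3. Bias by arithmetic.** Let d be the share missing in an arm and g the amount by which those missing do worse than those observed. Then bias = dA·gA − dC·gC. The values of d and g are assumed, except that 0.30 is the plan's allowance.

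- Equal loss and equal g: 0.
- 35% against 25% lost, g = 0.6 in both arms: 0.21 − 0.15 = 0.06, or 10% of the target.
- 30% lost in each arm, g = 0.6 in one arm only: 0.18, or 30% of the target. With no true effect and 70 per arm (SE = 1.2 × √(2/70) = 0.203), this bias raises the two-sided type I error from 5% to about 14%.

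**4. Bias by simulation.** Inputs: 100 per arm, SD 1.2, true difference 0.6, and about 30% monotone loss by month 12. The correlation of 0.7 between visits is assumed, as is loss with log-odds 0.8 per SD in one arm and random loss in the other. Estimated 12-month benefit of A over C:

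| Loss depends on | Arm | Raw 12-month | Change from baseline | Baseline-adjusted likelihood model |
|---|---|---|---|---|
| previous HbA1c | C | 0.40 | 0.63 | about 0.60 |
| previous HbA1c | A | 0.80 | 0.58 | about 0.60 |
| change since baseline | C | – | 0.53 | about 0.60 |
| change since baseline | A | – | 0.67 | about 0.60 |

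The bias is thus about 0.20 for raw values and about 0.02 to 0.07 for change; repeat runs gave 0.52 in the third row, a bias of 0.08. With the same pattern in both arms, the raw comparison was unbiased. I re-ran these settings and the figures held, apart from small shifts in the second decimal.

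**5. Precision under random loss, 70 per arm analysed.**

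- Raw: 1.2 × √(2/70) = 0.203.
- Change: 1.2 × √(2 × (1 − 0.7)) × √(2/70) = 0.157.
- Baseline-adjusted, 12-month values only: 1.2 × √(1 − 0.7²) × √(2/70) = 0.145.
- Likelihood model with all visits (simulated): about 0.142.

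Most of the gain in precision comes from adjusting for baseline. The intermediate visits add a little precision, and they are what protects against loss that follows earlier values.

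**The case against.** The strongest reply is that a journal article condenses a fuller protocol, and that the method for missing data is commonly left to that document or to the SAP. That stands as far as it goes: silence on imputation is not the point here. The point is that the methods the article does choose fit poorly with its own principle and its own allowance for loss.

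Several stronger readings are tempting, and the article does not support them.

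- *The primary result becomes a completers' analysis.* No such analysis is stated. Missing data are to be examined, and imputation before the named tests is not excluded. Nor does the text say t-test or repeated-measures ANOVA; both are inferences.
- *Thirty per cent will have no value.* The 30% covers compliance and drop-out together. A participant who does not comply but attends still gives an HbA1c, so 30% is an upper bound.
- *Group C has only yearly contact.* Usual care means visits at least once a year, but the study measurements are scheduled equally in all three groups, and A's consultations coincide with them. Support differs; scheduled measurement does not.
- *A third of the effect would be lost.* That holds only for a raw 12-month comparison with strong outcome-related loss in one arm. The plan also names analysis of changes, where the bias is much smaller.

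A mixed model is also not the only sound answer: multiple imputation before the named tests could serve.

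**Conclusion.** The point holds in a limited form. As written, the named tests use only participants with the needed HbA1c value, ignore earlier values of those lost before month 12, and do not by themselves give the intention-to-treat comparison. This creates a risk of bias, not a certainty. The bias is nil if loss and its relation to outcome are the same in both arms. Under the assumed one-arm pattern it is about 0.2 of the 0.6 target for raw values and about 0.02 to 0.08 for change from baseline. These sizes rest on a correlation of 0.7, on the full 30% being missing, on the assumed strength of the drop-out relation, and on reading the target and SD as HbA1c percentage points. The likelihood model stayed near 0.60 in the same scenarios, where loss depended only on observed values, as the model assumes. Since the primary outcome is affected and the remedy is cheap, the change should be made.

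**What to change.** Name as primary analysis a likelihood-based mixed model for repeated measures on all randomised participants in their assigned groups. The outcomes are HbA1c at week 12 and months 6, 12 and 24. The terms are baseline HbA1c, visit, group, group-by-visit and gender, the stratification factor given under Procedure and timeline. Read off the 12-month A–B and A–C contrasts.

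Add one sensitivity analysis for data missing not at random, for example imputing values after drop-out and worsening them by a fixed amount. A participant with only a baseline value gives no outcome to the model above, so the imputation should include such participants.

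The cost is somewhat more analysis work, which the mixed-model procedure in the planned software can handle, and reliance on missing-at-random, which is why the sensitivity analysis is needed. No new data or visits are required.

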### Procedure and timeline

The baseline measurements start with an examination by the patient’s general practitioner for exclusion purposes. A notification is made on subjects not fulfilling the criteria at this stage. The study-specific measurements are made by the diabetes specialist nurse or a trained assistant, followed by randomization to three groups using closed envelopes while stratified by gender. The participants are randomly assigned to either the multi-component intervention group (A), the single component group (B) or a control group (C). A total of 310 patients with pre- diabetes or type 2 diabetes will be included gradually, with the aim of 100 participants included in group A and B, and 110 in the control group C by the end of 2017. After randomization, participants are given a schedule for measurement time points and group A participants receive a schedule for group sessions and individual consultations. The intervention lasts for 24 months, with more intensive support from the health care professionals within the first 24 weeks, and less support in the second year (Fig. 2).

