### Limitations

Individuals with pre-diabetes and diabetes are randomized in the same group and it can be discussed whether the same decline in HbA_1c_ can be expected in individuals with pre-diabetes. Furthermore the participants in the control group may be influenced by participating in a research study and being assessed regularly. As they agree to join they are highly motivated to change their physical activity level and we expect many of them to succeed in this by their own. This could make comparison of between-group differences problematic. Moreover, the control group is assessed by the same staff as group A and B, for practical and financial reasons. This staff is trained in motivational interviewing and it might be difficult to treat the patients differently. At measurements participants from group A, B and C are given different schedules, group A participants are offered more time and a systematic motivational interviewing following a set of questions.

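### Covariates are to be used only if the groups differ at baseline, so chance and analyst judgement pick the primary HbA1c model and the precision from baseline HbA1c may be lost

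*Protocol article*

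**What the plan says.** Under *Sample size and planned statistical analysis*, the protocol article gives its adjustment rule in one sentence: "Potential confounders as (e.g. BMI at baseline, gender and age) will be used if there are differences at baseline". It names no test, threshold or closed list, and nothing elsewhere in the article replaces the rule.

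The same section describes the comparisons: "Un-paired and paired tests, correlation coefficients as well as ANOVAs will be used to assess the bivariate effects of the interventions", and adds that they serve "to analyze within-group and between-group differences and changes". It does not say whether the primary test is on the follow-up value or on the change, and it names no covariate-adjusted model for HbA1c.

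Three other places bear on the rule:
- *Procedure and timeline* describes "randomization to three groups using closed envelopes while stratified by gender". Gender is therefore a design factor, yet it appears in the analysis only as a conditional covariate.
- Table 1 schedules HbA1c, the primary outcome, at baseline, week 12 and months 6, 12 and 24, so a baseline value is planned for every participant.
- *Limitations* notes that "Individuals with pre-diabetes and diabetes are randomized in the same group" and that "it can be discussed whether the same decline in HbA_1c_ can be expected in individuals with pre-diabetes". Diabetes status is known from the inclusion criteria.

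**The concern.** Confounding by baseline variables is a problem of non-randomised comparisons. After proper randomisation, any baseline difference between groups A, B and C is chance. A covariate earns its place in the model by predicting the outcome, whether or not it is balanced. A rule triggered by imbalance has three consequences.

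1. The model behind the primary result varies from one realisation of the trial to another. With no criterion stated, it also depends on a judgement made after the baseline table has been seen.
2. The rule works against the design. Stratification exists to prevent a gender imbalance, so the rule will tend to leave gender out although the randomisation used it.
3. Baseline HbA1c, which would be expected to be the main predictor of later HbA1c, could enter through the open list, but only when it happened to be imbalanced. In most realisations its precision would be discarded.

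At stake is the precision of the primary comparison, in a trial whose stated 56 evaluable patients per group leaves little room.

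**Working it through.** **Inputs from the article:** difference 0.6, SD 1.2, 80% power, 56 per group, comparison at 12 months (*Sample size and planned statistical analysis*).

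**Assumptions, not in the article:** alpha 0.05 two-sided; 0.6 and 1.2 on one scale, although the text gives mmol/mol for one and % for the other, so d = 0.6/1.2 = 0.5; equal variance at baseline and follow-up; baseline-to-follow-up correlation r of 0.5 to 0.8.

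**Step 1: the plan's own figure.** n per group = 2 × (1.960 + 0.842)² × (1.2/0.6)² = 62.8, so 63, not 56. One-sided it is 50. At n = 56, power = Φ(0.5 × √(56/2) − 1.96) = Φ(0.686) = 75.4%. The stated 56 therefore does not reproduce under these assumptions. That is a separate matter, but it makes 75% the unadjusted reference below.

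**Step 2: variance factors.** Relative to the variance of the 12-month value:
- follow-up value only: 1
- change score: 2(1 − r)
- ANCOVA on baseline: 1 − r²

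Relative to the variance of change, ANCOVA has factor (1 − r²)/(2(1 − r)) = (1 + r)/2.

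**Step 3: power at 56 per group,** Φ(0.5/√factor × √28 − 1.96).

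If 1.2 is the SD of the 12-month value:

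| r | Follow-up only | Change score | ANCOVA | ANCOVA minus change |
|---|---|---|---|---|
| 0.5 | 75.4% | 75.4% | 86.3% | 10.9 points |
| 0.6 | 75.4% | 84.1% | 91.1% | 7.0 points |
| 0.7 | 75.4% | 92.7% | 95.9% | 3.2 points |
| 0.8 | 75.4% | 98.7% | 99.3% | 0.6 points |

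If 1.2 is the SD of change, the change-score test has 75.4%. ANCOVA, with factors 0.75, 0.80, 0.85 and 0.90, has about 86%, 84%, 82% and 80%.

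**Step 4: the conditional rule itself.** In a simulation of 20,000 two-arm trials (56 per arm, true difference 0.5 SD of the 12-month value), baseline was adjusted for only when its own test gave p < 0.05. That threshold is assumed, as the article gives none.

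| r, outcome tested | Power, conditional rule | Power, always adjusted | Type I error, conditional rule |
|---|---|---|---|
| 0.5, follow-up value | 75.9% | 85.4% | 0.044 |
| 0.5, change | 75.7% | 85.3% | 0.044 |
| 0.7, follow-up value | 77.0% | 95.4% | 0.034 |
| 0.7, change | 92.8% | 95.5% | 0.045 |

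The rule recovers almost none of the gain, because it seldom triggers adjustment. Its type I error lies below 0.05.

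**Step 5: how often chance would change the model.** If the three named covariates were each tested at 5% and were independent (both assumed), at least one would trigger adjustment in 1 − 0.95³ = 14% of perfectly randomised pairwise comparisons. Because gender is stratified, BMI and age alone are nearer the mark: 1 − 0.95² = 10%.

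**The case against.** **Much of this belongs in an SAP.** A condensed article need not print a full model, and the open list does not exclude baseline HbA1c or diabetes status. That is fair: their absence from the list is not a fault by itself. The trigger, however, is stated, and under it any covariate enters only conditionally.

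**The power gain looks smaller against change scores.** The plan allows analysis of changes. A reader who set ANCOVA only against a follow-up-only comparison might infer a gain from 75% to as much as 99%. Against change scores the gain is about 11 points at r = 0.5 and under 1 point at r = 0.8. This stands, and both comparators are needed.

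**Error rates.** A reader might infer that a data-driven model inflates false positives. The simulation does not support this: followed strictly, the rule is slightly conservative. What remains is discretion, because no strict rule is written down.

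**Gender.** Stratification already balances it, and no numerical consequence of leaving it out has been shown. This stands. Gender belongs in the model because the design used it, not because of a demonstrated loss.

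**Paired tests.** Paired tests are listed among the methods for assessing intervention effects, and of the control participants the authors write "we expect many of them to succeed in this by their own". A reader might infer that a significant change within group A or B will be claimed as an effect. The text does not require that. The natural reading matches paired tests to within-group description, and *Limitations* itself treats the between-group comparison as the one that matters.

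**Conclusion.** The point holds as a fault in a stated rule. Selecting covariates by observed baseline difference, with no criterion and an open list, leaves the primary HbA1c model to chance and to judgement after the data are seen. It also makes the use of baseline HbA1c conditional on imbalance.

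The demonstrated harm is loss of precision. Its size runs from under 1 to about 11 percentage points of power against change scores, and from about 11 to 24 points against follow-up values alone, if 1.2 is the SD of the 12-month value. If 1.2 is the SD of change, the loss is about 4 to 11 points. All of these rest on the assumed alpha, common unit and correlation range.

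Randomisation still protects the comparison, and inflated type I error is not shown. The doubt about equal response in pre-diabetes makes diabetes status a sensible prognostic covariate; it does not oblige the plan to test an interaction. This should be fixed, but it does not invalidate the trial.

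**What to change.** Delete the sentence that ties adjustment to baseline differences. In its place, name one between-group model for HbA1c at the time point the sample size uses (12 months), always adjusted for:
- baseline HbA1c;
- gender, as the stratification factor;
- diabetes status (pre-diabetes or type 2 diabetes), as a prognostic factor known at entry.

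State that this set applies whatever the baseline table shows, and that conclusions about intervention effects rest on the between-group contrasts from this model, with within-group changes reported descriptively. A treatment-by-diabetes-status term may be added as a secondary analysis but is optional.

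The cost is wording, agreed before the outcome data are analysed. All the variables are already planned for collection or known at entry, and no extra patients or visits are needed.
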